### Data collection and management

The data collection schedule is presented in table 1. In this phase, data collection will be conducted through repeated assessment interviews at baseline (month 0), the end of the intervention (month 4) and 2 months after the intervention ended (month 6).

The questionnaires will be self-administered and collected via a tablet computer using Research Electronic Data Capture (REDCap) tools. The forms will be checked for completeness by a research assistant soon after completion, and errors will be corrected. The REDCap database resides within a single MySQL database server within a secure server cluster at AHRI. Interviews will be audio recorded and transferred into a password-protected computer for transcription.

### Data analysis

The primary outcome of this study is the feasibility and acceptability of the delivery of PM+Adherence among ALHIV in uMkhanyakude, KwaZulu-Natal. Feasibility will be determined using the following criteria: (1) reach will be assessed through 75% recruitment and consent rates; (2) adoption and retention, where enrolled participants attend ≥50% of sessions and complete assessments at 6 months; (3) implementation, where there is at least 75% fidelity to the protocol; (4) acceptability of the intervention will be assessed through semistructured interviews (see table 2). The proportion and 95% CI for each measure will be calculated.

**Table 2 T2:** Feasibility and acceptability measure

	Explanation	Time point	Criteria
Reach	Percentage of acceptance rate and number of adolescents recruited.	Baseline	At least 75% of the target population.
Adoption	Attendance of study participants to sessions and assessments throughout the trial.	During implementation	At least ≥50% of sessions attended.
Retention	Participants retention rates.	After implementation	A rate of 90% of participants attend the final assessment at 6 months.
Implementation	Through fidelity checklists, the research team will assess the adherence rate to the intervention protocol, including consistency of delivery as intended and the adolescents’ use of the intervention strategies.	During implementation	At least 75% or greater.
Acceptability of adapted intervention	Semistructured interviews assessing views of adolescents, facilitators and healthcare providers about the adapted intervention and implementation.	After implementation	Qualitative data will be coded for themes.

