### Sample size

One of the areas of focus addressed by feasibility studies is the reach (uptake) of an intervention by the intended audience.^73^ Reach considers the absolute number, proportion and representativeness of the target population willing to participate in a given intervention and the reasons why or why not.^87^ Feasibility studies are not expected to have large sample sizes; therefore, a precision estimate was made for our sample size.^74 88^ If the true proportion of those willing to enrol (reach) is 75%, a sample size of 67 approached and 50 enrolled would allow us to estimate this proportion with a precision of ±10%. If 90% of participants complete the study at 6 months, a sample size of 50 ALHIV will allow us to estimate adoption (participant retention) with a precision of ±8%.

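### The reach and retention pass marks equal the values the study expects, so a study that performs as planned often misses them, and the planned 50 of 67 is itself just below the reach mark

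*Protocol article*

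**What the plan says.** The Sample size section of the protocol article justifies the numbers by precision. For reach: "If the true proportion of those willing to enrol (reach) is 75%, a sample size of 67 approached and 50 enrolled" gives an estimate within ±10%. For retention: "If 90% of participants complete the study at 6 months", then "a sample size of 50 ALHIV will allow us to estimate adoption (participant retention) with a precision of ±8"%.

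The Data analysis section makes feasibility and acceptability the primary outcome and lists the criteria that determine feasibility. On reach, the text says "reach will be assessed through 75% recruitment and consent rates", and Table 2 says "At least 75% of the target population". On retention, Table 2 says "A rate of 90% of participants attend the final assessment at 6 months". The same section plans a proportion and a 95% CI for each measure.

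The article does not say whether the point estimate or the CI is set against each mark, or whether every mark must be met. It describes no zone between success and failure.

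**The concern.** A pass mark placed at the expected value cannot reliably recognise a study that performs as expected. The observed proportion falls above or below its true value by chance, so the result against the mark is close to a coin toss exactly where the sponsor would want a clear pass.

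Reach has a second problem that needs no probability model. The planned recruitment of 50 out of 67 falls below the study's own mark.

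The criteria matter because they determine the primary feasibility conclusion. The Phase 3 study design section says this phase is meant to show whether the adapted intervention is appropriate for further testing, and the Expected outcome section looks ahead to a randomised trial.

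**Working it through.** **Inputs.** From Sample size: assumed reach 0.75 with 67 approached and 50 enrolled; assumed retention 0.90 with n = 50. From Table 2: marks of at least 75% and 90%.

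**1. The plan's own precision figures.** Half-width = 1.96 × √(p(1 − p)/n).
- Reach: 1.96 × √(0.75 × 0.25/67) = 1.96 × 0.0529 = 0.104, against ±10% stated.
- Retention: 1.96 × √(0.90 × 0.10/50) = 1.96 × 0.0424 = 0.083, against ±8% stated.

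Both reproduce to whole points. The 67 is 50/0.75 = 66.7 rounded up.

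**2. Counts needed to meet the marks.**
- Reach: 0.75 × 67 = 50.25, so 51 are needed. The planned 50/67 = 74.6% falls one short.
- Retention: 0.90 × 50 = 45, so 45 of 50 is exactly on the mark and passes.

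**3. Chance of meeting each mark when the truth is as planned.** Exact binomial upper tails, comparing the observed proportion with the mark:

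| Measure | True rate | Needed | Pass | Miss |
|---|---|---|---|---|
| Reach, strict | 75% | ≥51/67 | 0.481 | 52% |
| Reach, 74.6% rounded to 75% | 75% | ≥50/67 | 0.592 | 41% |
| Retention | 90% | ≥45/50 | 0.616 | 38% |

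**4. Both marks together, if both are required and independent.**
- Strict reach: 0.481 × 0.616 = 0.297, so at least one is missed about 70% of the time.
- Rounded reach: 0.592 × 0.616 = 0.365, so 63%.
- If the number enrolled varies with reach instead of being fixed at 50, the pass chances are 0.269 (strict) and 0.337 (rounded), so misses of 73% and 66%.

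**5. Discrimination around the marks.** With ≥51/67, a true reach of 70% passes 17% of the time and a true reach of 80% misses 17% of the time. With ≥45/50, a true retention of 85% passes 22% of the time.

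**6. If the CI were set against the same marks.** Requiring the lower 95% Clopper–Pearson limit to reach 75% or 90% would take 58/67 or 50/50. At the planned rates these have chances of 1.6% and 0.5%. Bringing in the CI without lowering the marks would therefore make matters worse.

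**7. An illustrative alternative.** Suppose the lower Wilson 95% limit must be at least 60% for reach and 75% for retention.
- Reach: 49/67 gives a lower limit of 61.5%, and 48/67 gives 59.9%, so ≥49 is needed. Pass chance 0.70 at true 75% and 0.018 at true 60%.
- Retention: 44/50 gives 76.2%, and 43/50 gives 73.8%, so ≥44 is needed. Pass chance 0.77 at true 90% and 0.019 at true 75%.
- Jointly, if independent: 0.70 × 0.77 = 0.54 at the planned rates, compared with 0.30 now.

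**The case against.** The best reply is that the decision rule tested here is not written in the article. It gives criteria and plans CIs, but does not say that the point estimate alone decides, that every criterion must be met, or that one miss stops progression. Those details may sit in the full protocol or analysis plan. This stands: the figures in steps 3 to 5 depend on comparing the observed proportion with the mark, and the 70% also depends on requiring both. What it does not answer is that the numerical marks are fixed in the article, equal the planning values, and are said to determine feasibility.

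A reader might infer that each measure fails about half the time or more. The numbers do not support that for retention alone, which misses 38%. A reader might also infer that the CIs are excluded from the decision, or that a missed mark blocks the future trial. The article says neither.

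The reach denominator can also be questioned. Table 2 refers to the target population, the text to recruitment and consent rates, and Study outcomes to enrolled among approached. The figures here use enrolled out of 67 approached, as Sample size does.

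Finally, the 50/67 shortfall is a rounding matter of 0.4 percentage points. That is fair as to size. Yet rounding it away still leaves reach missed 41% of the time, and changing to 50/66 gives a pass chance of only 0.51. The arithmetic slip is the smaller part of the problem.

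**Conclusion.** The point holds as a flaw in how the pass marks are set, and it should be fixed. The main result is a 52% chance of missing reach and a 38% chance of missing retention when the true rates are as planned. The figure of about 70% for missing at least one rests on two assumptions that the article does not state: both are required, and they are independent. The adoption, fidelity and acceptability criteria are left out; requiring them too could not lower the chance of a miss.

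It would be too strong to call this a must-fix error or to say that the sample size is wrong. The precision justification is sound, no estimate is biased, and the proportions with their CIs will be informative whatever the marks are. What is weak is the verdict drawn from them.

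**What to change.** Keep 75% and 90% in Sample size as expected values. In Table 2, have the sponsor prespecify a lower minimum acceptable value for reach and for retention. Judge each against the 95% CI already planned, with an intermediate zone in which the programme is modified and then proceeds. State whether all criteria must be met.

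The floors of 60% and 75% in step 7 are illustrations only; they have no source in the article, and the sponsor should choose its own. Even with them, a study performing as planned misses a full pass on both measures about 46% of the time, which is why the intermediate zone is needed.

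Separately, reconcile the recruitment figures with the 75% mark: 51 of 67 (76.1%) or 50 of 66 (75.8%). This removes the inconsistency but does not by itself improve the decision rule.

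The cost is a revised criterion for each of the two measures in Table 2 and a sentence or two of text, with no added participants. The stated criteria will look slightly less ambitious.

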#### Quantitative data

Secondary outcomes will be assessed by comparing measurements before and after the intervention. Continuous outcomes (eg, viral load, mental health) will be analysed using paired t-tests. Logistic regression will be used to estimate the OR and 95% CIs for the association of self-reported adherence measures with VL suppression. Analysis will be conducted using STATA V.18, and statistical significance based on p<0.05.

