#### Study population

We will recruit adolescents (target sample size n=50) living with HIV and receiving care at AHRI-supported clinics. A random sample of 67 potential participants (ensuring gender balance) who are aware of their HIV status and have agreed to future contact with the AHRI team will be selected from the existing AHRI Demographic Information System (ACDIS) database, and they will be approached and invited to enrol. Adolescents will be included in the study if they are aged 16–19 at the time of recruitment, reside in uMkhanyakude at the time of recruitment, have a score of ≥10 on the Patient Health Questionnaire (PHQ-9) or Generalised Anxiety Disorder Scale (GAD-7) and provide informed consent. We will exclude individuals with a self-reported history of severe mental illness, including psychotic-related disorders, bipolar disorders, eating disorders and substance dependence, as well as those with cognitive deficits (assessed using the Mini-Mental Status Examination),^76^ those presenting with suicidal ideation or judged to be at active risk of suicide (as assessed using the Columbia-Suicide Severity Rating Scale), and those undergoing active psychiatric treatment (ie, on psychotropic medication or receiving formal psychotherapy).

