#### Secondary outcomes

HIV-related outcomes include viral suppression (VL) using dried blood spots and adherence will be assessed using the Adolescent Master Protocol questionnaire, an adaptation of a self-reported adherence questionnaire that measures the number of missed doses. We will also assess the validity of these scales in our study population. Mental health and well-being outcomes will be assessed using the PHQ-9,^78 79^ GAD-7,^80 81^ Patient-Reported Outcomes Information System Sleep Disturbance Scale,^82 83^ Child and Youth Resilience Measure^84 85^ and Personal Well-Being Score.^86^

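### Logistic regression of viral suppression on self-reported adherence in about 45 to 50 adolescents would be less biased, and always finite, if Firth's penalised likelihood were named; a minor, low-cost improvement

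*Protocol article*

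**What the plan says.** The Quantitative data section gives one analysis that relates self-report to viral load: "Logistic regression will be used to estimate the OR and 95% CIs for the association of self-reported adherence measures with VL suppression". It names Stata 18 and sets "statistical significance based on p<0.05". It names no estimator and no type of confidence interval.

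The rest of the article fixes the data for this model:

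- **Size.** Under Study population: "We will recruit adolescents (target sample size n=50) living with HIV and receiving care at AHRI-supported clinics". The Sample size section works with 90% completing six months, which is 0.90 × 50 = 45.
- **Visits.** In Table 1, viral suppression is measured at months 0 and 6 only, and adherence at months 0, 4 and 6. The two can be paired only at months 0 and 6.
- **Predictor.** Under Secondary outcomes, the instrument is "an adaptation of a self-reported adherence questionnaire that measures the number of missed doses". No yes/no cut is stated. The same section says that the validity of the scales will be assessed.
- **Outcome frequency.** No expected proportion suppressed or unsuppressed appears anywhere.

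**The concern.** The information in a logistic model depends on the size of the smaller outcome group, not on the total sample. With 45 participants, 10% unsuppressed is 4 or 5 people and 20% is 9. At such counts maximum likelihood has two known weaknesses:

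1. The odds ratio is biased away from 1.
2. If the predictor separates the outcomes (for a yes/no predictor, if a cell of the 2×2 table is empty), no finite estimate exists.

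This is the only stated quantitative analysis that asks whether self-reported adherence tracks viral suppression. An inflated odds ratio would make self-report look better than it is, and an infinite one could not be used. A switch of method after the problem has been seen would be post hoc. Naming a more robust estimator beforehand avoids that.

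**Working it through.** **The plan's own figures.** The article states no figure for the logistic model. Its two precision statements reproduce with 1.96 × √(p(1−p)/n):

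- Reach: 1.96 × √(0.75 × 0.25/67) = 0.104 (stated as ±10%).
- Retention: 1.96 × √(0.90 × 0.10/50) = 0.083 (stated as ±8%).

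They confirm the sample sizes used below but say nothing about the logistic model.

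**Inputs.** From the article: n = 50 at baseline, 45 at month 6, and a count of missed doses. Assumed, because the article gives none of them: proportion unsuppressed 5% to 30%, true odds ratio 3, the shape of the count distribution and, for a yes/no split, 20% to 40% reporting missed doses.

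**A. Missed doses kept as a count (the measure the article describes).** Simulation with n = 45, a skewed (negative binomial) count scaled to one standard deviation, a true odds ratio of 3 per standard deviation for being unsuppressed, and 4,000 datasets per row. The rows below use mean 2 and dispersion 0.5. Odds ratios are geometric means. Maximum likelihood (ML) is averaged over datasets without separation, and Firth over all datasets.

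| Unsuppressed | Separation | ML OR | Firth OR | RMSE of log OR, ML | RMSE of log OR, Firth |
|---|---|---|---|---|---|
| 10% | 6.7% | 3.62 | 3.07 | 0.84 | 0.64 |
| 20% | 0.2% | 3.50 | 3.01 | 0.64 | 0.52 |
| 30% | 0.0% | 3.48 | 2.99 | 0.63 | 0.53 |

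- Inflation of the ML odds ratio: 3.62/3 = 1.21, 3.50/3 = 1.17 and 3.48/3 = 1.16. Two other count shapes (mean 2 or 1, dispersion 1) gave 3.44 to 3.55, that is 1.15 to 1.18. Overall this is roughly 15% to 20%.
- The two averages cover different sets of datasets, so Firth was also averaged over only those where ML exists. It gave 2.93, 3.00 and 2.99 in the three rows, so the contrast does not come from that difference.
- The reduction in root-mean-square error (RMSE) in these rows is 24%, 19% and 16%. Across the count shapes tried it was about 13% to 26%.
- At 5% unsuppressed, separation rises to about 26% to 30% with these counts.

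**B. Adherence split yes/no (not stated in the article).** Let q be the share reporting missed doses, and p1 and p0 the probabilities of being unsuppressed with and without missed doses. Ignoring the two large cells, which are almost never empty in this example:

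P(empty cell) ≈ (1 − q·p1)^n + (1 − (1−q)·p0)^n − (1 − u)^n, where u = q·p1 + (1−q)·p0 is the overall proportion unsuppressed.

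Example with n = 50, q = 0.3, u = 0.10 and odds ratio 3: p0 = 0.0669 and p1 = 0.1771, so q·p1 = 0.0531 and (1−q)·p0 = 0.0469. Then 0.9469^50 + 0.9531^50 − 0.90^50 = 0.065 + 0.091 − 0.005 = 0.151.

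Over n = 45 and 50 and q = 0.2, 0.3 and 0.4, with all four cells counted:

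| Unsuppressed | P(empty cell) |
|---|---|
| 5% | 49.1% to 58.1% |
| 10% | 15.1% to 23.5% |
| 15% | 4.1% to 8.6% |
| 20% | 1.0% to 3.8% |
| 30% | 0.1% to 1.7% |

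**C. What each remedy does with an empty cell.** Take 5 of 15 unsuppressed among those with missed doses and 0 of 30 among the rest.

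- Maximum likelihood: the odds ratio is infinite.
- Firth, which for a 2×2 table adds 0.5 to each cell: (5.5 × 30.5)/(10.5 × 0.5) = 32.0. The standard error of the log is √(1/5.5 + 1/10.5 + 1/0.5 + 1/30.5) = 1.52, so the Wald 95% interval is 1.6 to 628. It is finite but very wide.
- Exact conditional: the 95% interval runs from 2.2 to infinity.

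**The case against.** The strongest case against the point has five parts.

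- **The estimator is not named.** Firth regression is also logistic regression and would satisfy the sentence as written. A condensed article may leave the estimator to an analysis plan that is not shown. This stands in part: the article does not rule out Firth, so nothing in it is contradicted. But the bare name of the method conventionally means maximum likelihood, and the point offers a better stated choice rather than complaining of a missing detail.
- **The unsuppressed proportion is unknown.** A reader might infer that the odds ratio will often be infinite or undefined. The documents do not support that. They give no rate, and they point both ways. All participants are in clinic care, but all must also score at least 10 on the PHQ-9 or GAD-7, and the Introduction links mental health problems to poorer adherence. At 20% or more unsuppressed, failure is uncommon to rare.
- **The predictor is a count.** The empty-cell figures for a yes/no split describe an analysis that the article does not state. This stands, and it is why the main result here is the bias with a count.
- **Firth does not rescue an uninformative sample.** This also stands: an interval of 1.6 to 628 says little. The gain is a finite estimate and less bias, not precision.
- **The stakes are small.** This is one secondary association in a feasibility study that the article says is not powered for efficacy, and no feasibility criterion depends on it. That limits the importance of the point, but it is no reason to prefer the more biased estimator when the alternative costs one sentence.

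**Conclusion.** The point holds as a minor improvement to one secondary analysis. With about 45 adolescents and missed doses analysed as a count, maximum likelihood would overstate an assumed true odds ratio of 3 by roughly 15% to 20% at 10% to 30% unsuppressed. Firth would be close to unbiased, with a smaller overall error. Failure to estimate is a secondary risk. It is uncommon with a count unless about 5% or fewer are unsuppressed, and it becomes material with a yes/no split at about 10% or fewer.

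All sizes rest on assumptions about the unsuppressed proportion, the true odds ratio and the distribution of missed doses, none of which the article gives. Two stronger readings should be avoided: that the plan contains an error, and that exact logistic regression would serve equally well. An exact interval keeps an infinite limit when a cell is empty, so it does not solve the problem.

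**What to change.** In the Quantitative data section, state that the association will be estimated by Firth penalised-likelihood logistic regression with a profile-likelihood 95% confidence interval, one adherence measure per model, fitted separately at months 0 and 6. Do not list exact logistic regression as an equal alternative. Report the number unsuppressed at each visit beside the odds ratio. If that number is zero, report only the counts: with 0 of 15 against 0 of 30, Firth would return (0.5 × 30.5)/(15.5 × 0.5) = 1.97, which reflects the penalty and not the data.

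The cost is one sentence, a slightly less familiar method and estimates drawn a little toward 1. Intervals will remain wide because the sample is small. No change to recruitment, visits or measurements is needed.

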#### Qualitative data

Transcripts from the interviews and focus group discussions will be transcribed and translated where necessary. The coding and management of data will be conducted using NVivo software.^89^ The transcripts will be coded using an inductive approach, allowing themes to emerge organically from the discussions. Their experience of the PM+Adherence intervention will be of interest, as will the identification of facilitators and barriers to engaging in the intervention and systemic related factors that provide support.

### Risk assessment and management

During screening, any potential participant identified as experiencing suicidal ideation using the Columbia Suicide Severity Rating Scale will be referred for further clinical/risk assessment by an AHRI clinical psychologist. The clinical psychologist will assess whether these are significant by considering a range of well-established factors, including history of suicidality, number of prior attempts, intention and plans. The psychologist will then decide whether they can continue with the study or require more specialised services. Although this study will not include them, we will link them with the appropriate services. Those identified with other challenges, in line with the AHRI Child Protection Standard, will be linked with the Child Protection Lead at AHRI for assessment, who will advise on further management where possible. Adverse events and serious adverse events will be closely monitored during each visit. In consultation with the Child Protection Lead, the principal investigator will determine whether these events may be related to the study and report to mentors, who will function as a monitoring board when necessary. The research assistants and facilitators will record and report these events to the study team, and serious adverse events will be reported to the ethical review committee.

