#### Participant timeline

Participants will be involved in the study for 6 months. Participants will complete assessments at baseline before the intervention is delivered. The intervention will be delivered over approximately 4 months, with sessions held every fortnight at the participant’s home or elsewhere. The decision to have the sessions fortnightly was due to expert feedback from local clinicians who indicated that every week would be burdensome to the young people as they need to also attend school in between clinic appointments. After completion of the intervention, participants will be scheduled for follow-up assessments at the endpoint (month 4) and 2 months post-intervention (month 6).

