#### Training

Two types of training will be conducted in preparation for implementing the adapted PM+Adherence intervention. One is for research assistants (3), and another is for the intervention facilitators and lay counsellors (5). Research assistants will support the implementation of the study, including participant recruitment, collecting informed consent and outcome assessments. The research assistants will be individuals between the ages of 24 and 30 years, with a minimum bachelor’s degree, fluent in isiZulu. The research assistants’ training will cover the study’s background, methodologies, expected benefits and potential risks to participants, outcome assessment tools, administration of questionnaires and interviews, electronic data capture tools, the importance of data quality and consenting procedures. This training will be performed with the support of the AHRI Data Management team. The research assistants will also be trained on how to assess for risk, as well as monitor and record adverse and serious adverse events. For facilitators (lay counsellors) who deliver the PM+Adherence intervention, two pieces of training will be carried out in preparation for implementation. A 2-week training of trainers (ToT) workshop will be held for two trainers (both psychologists) to consider isiZulu language adaptations. The trainers will conduct supervised practice (role-play) and qualitative feedback will be collected during a debriefing session after training. A 3-month training of lay counsellors will follow ToT training. This length of time was based on previous studies using lay counsellors. The lay counsellors will be individuals between the ages of 24 and 30 years, with a minimum of matric (in South Africa, this is the grade 12 high school graduation certificate), lived experience of HIV or mental illness, from the local community with previous experience in community engagements/support. The training of lay counsellors will involve a combination of classroom and field support, followed by supervised practice in which facilitators will deliver the intervention to young people. The trainers will rate lay counsellors on fidelity and competency (ie, whether they completed each component of the session, how well they delivered the session, use of group facilitation skills, basic helping skills and how to manage acutely distressed participants). Lay counsellors will also be trained to complete self-report fidelity checklists of the intervention components. The intervention will be delivered face to face. They will also be trained to assess for risk and monitor and record adverse and serious adverse events. All research assistants and lay counsellors will be trained in safeguarding participants. The Ensuring Quality in Psychological Support platform will be consulted to select appropriate assessment tools, including WeACT–Foundational Helping Competencies for Children and Adolescents and the PM+ Competencies assessment tool.^77^

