##### Drop-outs

Prior to the start of the intervention, contact details of the adolescent and a significant other (caregiver/friend) will be collected. During the intervention, if a participant misses a scheduled intervention session, the research staff will contact them by phone (up to three times before they are considered lost to follow-up) to book an alternative appointment to enhance retention. Our adoption criteria is at least ≥50% of sessions attended. At the end of the intervention, to understand the reasons for participant drop-out, we will make two attempts to call or visit participants who did not complete the intervention at home.

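### The article states visits as the only occasion for adverse-event monitoring and gives the contacts with non-attenders other purposes, so harms in participants who stop attending may be missed

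*Protocol article*

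**What the plan says.** **When harms are monitored.** Protocol article, Risk assessment and management: "Adverse events and serious adverse events will be closely monitored during each visit". The same section adds: "The research assistants and facilitators will record and report these events to the study team". Under Training, the lay counsellors' preparation includes this: "They will also be trained to assess for risk and monitor and record adverse and serious adverse events". Research assistants receive equivalent training.

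**What happens to non-attenders.** The Drop-outs section describes two contacts.
- After a missed session, "the research staff will contact them by phone (up to three times before they are considered lost to follow-up) to book an alternative appointment". The stated aim is to improve retention.
- Later there is a contact with non-completers: "At the end of the intervention, to understand the reasons for participant drop-out, we will make two attempts to call or visit participants".

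**Which visits exist.** Participant timeline describes the intervention "with sessions held every fortnight at the participant’s home or elsewhere", with assessments at month 4 and month 6. Table 1 schedules the PHQ-9 and GAD-7 at baseline, month 4 and month 6, and has no row for adverse events.

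**The concern.** Between baseline and month 4, the sessions are the only visits described. A participant who stops attending therefore has no stated occasion for harms to be asked about until month 4. The two contacts that could fill the gap are assigned to rebooking and to reasons for leaving.

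Everyone enrolled scores at least 10 on the PHQ-9 or GAD-7. In such a group it is plausible, though the article does not document it, that some who worsen will stop coming. Missing harms would then not be a random subset, and the reported frequency could be too low. The study is meant to show whether the adapted intervention merits further testing, and a randomised trial is foreseen, so its account of harms should cover everyone enrolled as far as possible.

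**Working it through.** **No adverse-event figure to reproduce.** The article gives no expected event rate and no precision for harms. The nearest figure is the retention precision in Sample size: 1.96 × √(0.90 × 0.10 / 50) = 0.083, which matches the stated ±8%. It neither supports nor weakens this point. It supplies only the planning values: 50 enrolled and 90% retained, so 45 seen at month 6 and 5 not.

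**Stated purpose of each contact**

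| Contact | Stated purpose | Harms mentioned? |
|---|---|---|
| Session or assessment visit | Intervention or outcomes | Yes, at each visit |
| Calls after a missed session | Rebooking, retention | No |
| End-of-intervention call or visit to non-completers | Reasons for drop-out | No |

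**Length of the gap**
- Inputs: seven fortnightly sessions (Intervention); next assessment at month 4, about week 17.4 (Participant timeline).
- With session 1 at week 0 (an assumption), sessions fall at weeks 0, 2, 4, …, 12.
- Leaving after session 2: 17.4 − 2 = 15.4, about 15 weeks to month 4.
- Leaving after session 4, which meets the 50% attendance criterion (4/7 = 57%): 17.4 − 6 = 11.4, about 11 weeks.
- The article says only that a date is set after baseline, so session 1 may be later. If session 7 falls exactly at month 4, session 2 is at 17.4 − 10 = week 7.4 and the gap is 10 weeks. The 15 weeks is therefore the upper end for someone leaving after session 2.
- These gaps apply to someone who returns for the month-4 assessment. For someone lost to follow-up there is no later visit.

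**Share of affected participants missed (illustration)**

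Formula: share missed = n_d·p_d / (n_r·p_r + n_d·p_d), where n_d and n_r are the numbers lost and retained, and p_d and p_r their event risks. All risks are assumptions, as is the premise that no event is observed in those lost.

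With n_d = 5, n_r = 45 and p_r = 10% (4.5 affected among the retained):

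| p_d | Affected among lost | Share missed | True proportion of 50 |
|---|---|---|---|
| 10% | 0.5 | 0.5/5.0 = 10% | 10% |
| 20% | 1.0 | 1.0/5.5 = 18% | 11% |
| 30% | 1.5 | 1.5/6.0 = 25% | 12% |
| 50% | 2.5 | 2.5/7.0 = 36% | 14% |

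The proportion observed among those assessed stays at 4.5/45 = 10% throughout, so the understatement is 0 to 4 percentage points. Dividing by all 50 would give 4.5/50 = 9%, which is why the number assessed must be reported. With 20% drop-out (n_d = 10, n_r = 40), the share missed runs from 1/5 = 20% to 5/9 = 56%.

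**The case against.** The case on the other side has real force on several points.

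- **The text does not restrict collection to visits.** A reader might infer that events are collected only there. The article names one occasion without excluding others. Staff are trained to record events with no limit to visits, and the study commits to Good Clinical Practice. This stands: harms may be missed, but it does not follow that they will go unrecorded.
- **The drop-out contact may reveal harm.** Asking why someone left can bring out that they worsened, and a home visit could count as a visit. This also stands, but it depends on a volunteered answer where a direct question would cost little.
- **Stopping sessions is not leaving the study.** The month-4 and month-6 assessments are scheduled separately, so some who stop sessions will be seen again. That is true, and it limits the gap for them. However, the Drop-outs section also treats a participant as lost to follow-up after up to three calls.
- **The record does not come mainly from those doing well.** A reader might infer that it does. Nothing in the article links attendance to outcome, and at planned retention about 45 of 50 are still seen at month 6.
- **No decision rule uses harms.** The feasibility criteria in Table 2 contain no adverse-event threshold, so an effect on the progression decision cannot be traced to a stated rule.
- **An article condenses.** Look-back periods on forms and tabulation by completion status may sit in the full protocol or analysis plan, and their absence is not held against the article. A fuller safety procedure may also exist. But the article does state the occasion for harms and the purpose of each contact, and as stated these leave the gap.

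**Conclusion.** The concern holds as a weakness in how harms are ascertained. Monitoring is stated for visits, and both planned contacts with non-attenders are given other purposes. A participant who leaves after session 2 may go up to about 15 weeks without a stated harms enquiry, assuming session 1 falls at week 0. One who is lost to follow-up may never be asked.

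Whether the loss is related to deterioration is plausible but not documented, and its size cannot be derived from the article. The 10% to 36% range is an illustration at 10% drop-out under assumed risks. For those risks it is an upper bound, because someone who misses month 6 may have had events recorded at earlier sessions or at month 4. The point justifies a change to the procedure. It does not support a claim that the safety record is known to be biased.

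**What to change.** - **Drop-outs:** state that the adverse-event questions staff already use are asked at each rebooking call that reaches the participant, and at the end-of-intervention contact with non-completers.
- **Risk assessment and management:** replace the visit-based wording with monitoring at each visit and each study contact, through month 6, for all enrolled participants whether or not they still attend sessions.
- **Reporting:** give harms together with the number of the 50 enrolled who were actually assessed for them.

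This changes data collection and reporting only. It uses contacts already planned and staff already trained. The cost is a few minutes per contact and wording in two sections. The reported event count will probably rise, and the write-up should say that this reflects fuller ascertainment.
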